### Data collection and management

Before the start of the study, all primary investigators at different centers will discuss the research protocol face-to-face or online. Meetings will be held to train researchers who will participate in the trial. The principal investigator of the research unit is responsible for the implementation and management of this clinical trial. Other researchers are responsible for clinical diagnosis/treatment, informed consent, screening, clinical sample collection, follow-up, data entry, etc. The pharmacy administrator of the research unit is responsible for the management of clinical trial drugs. A researcher will collect data through a prespecified case report form (CRF). The data should be accurate, complete, timely and reliable. A clinical trial associate will verify whether the data filled in the CRF are complete and accurate. EDC system is used to input data in CRF, which is proofread by data administrator. Interim analysis will not be adopted. The sponsor shall provide clinical inspectors for monitoring (1–2 times per month). An independent third-party company is responsible for the compilation of experimental drugs, data statistics, etc. All personal information of participants collected will be remained strictly confidential. The primary investigator has the access to the final trial dataset.

### Data analysis

An independent statistical analysis plan will be formulated. All analyses will be conducted in the full analysis set (FAS) population, defined as all patients randomized to an intervention group having at least one efficacy treatment after randomization. The outcomes will also be assessed in the per-protocol set (PPS). The results from FAS and PPS will be compared. Safety set will be used to evaluate the safety of experimental drug. The compliance of treatment and treatment-related withdrawals will be evaluated by arm. Participants’ characteristics and clinical measures will be described as the mean ± standard, median (interquartile range), or frequencies and percentages as appropriate. All statistical analyses will be performed using SAS, V.9.4. All statistical tests are bilateral tests. A *p* value ≤ 0.05 is considered statistically significant.

### Analysis of efficacy

The primary analysis will aim to compare the wound healing rate within 12 weeks between the pentoxifylline group and the control group by chi-squared test or Fisher’s exact test. The result will be expressed as risk ratio and 95% confidence interval. The wound healing rate at 4, 8, 16, and 24 weeks will be assessed by time-event analysis. Kaplan–Meier plot, Log-rank test, and Cox regression will also be used to analysis the time-to-event outcome, with the result of hazard ratio and 95% confidence interval. The covariates that should be adjusted in the Cox regression analysis include gender, age, duration of disease, BMI, pre-treatment ulcer area, compression therapy, and endovenous surgery. Last observation carried forward will be used to fill up the missing values if some primary outcomes may be missing.

The secondary analysis will compare the VCSS score, CIVIQ score, percent of wound size changes, and ulcer recurrence within 24 weeks by *t* test, Wilcoxon rank test, chi-squared test, or Fisher’s exact test as appropriate.

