### Inclusion criteria

To be eligible to participate in this study, a subject must meet all of the following criteria:Age ≥ 18 yearsMeeting the criteria of VLUs (patients with CVD and complicated with ulcers (level C6 of CEAP classification). The surface area of the VLU should be within the range of 1 cm^2^ and 20 cm^2^. If there are more than one ulcer in a subject, the ulcer with the largest area will be chosen as the index ulcer. The distance between the index ulcer and other ulcers should be more than 2 cm.Consciousness, without aphasia, able to eat drugsAnkle brachial index ≥ 0.7Written informed consent by participants or surrogate

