### Outcomes

#### Primary outcome

Wound healing rate within 12 weeks, expressed as the proportion of participants with complete wound healing of the index ulcer within 12 weeks. Complete wound healing is defined as full epithelialization of the wound without scarring [19].

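### The primary 12-week healing comparison is unadjusted although ulcer area and disease duration are already named as covariates: a modest loss of precision, not a power shortfall

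*Protocol article*

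**What the plan says.** All of this is in the Protocol article; a separate statistical analysis plan is announced under Data analysis but is not shown.

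- Primary outcome: the result is binary, "expressed as the proportion of participants with complete wound healing of the index ulcer within 12 weeks".
- Analysis of efficacy, primary: the plan is to "compare the wound healing rate within 12 weeks between the pentoxifylline group and the control group by chi-squared test" or Fisher's exact test. On the effect measure it says: "The result will be expressed as risk ratio and 95% confidence interval". No covariate is attached to either.
- Analysis of efficacy, time to healing: "The covariates that should be adjusted in the Cox regression analysis include gender, age, duration of disease, BMI, pre-treatment ulcer area", followed by compression therapy and endovenous surgery. The list belongs to the Cox regression only.
- Analysis of efficacy, secondary: "The secondary analysis will compare the VCSS score, CIVIQ score, percent of wound size changes, and ulcer recurrence within 24 weeks", to be done "by *t* test, Wilcoxon rank test, chi-squared test, or Fisher’s exact test as appropriate". Baseline values are not mentioned, and the text does not say whether VCSS and CIVIQ are compared as follow-up values or as changes.
- Inclusion criteria: "The surface area of the VLU should be within the range of 1 cm^2^ and 20 cm^2".
- Randomization and allocation concealment: 1:1 allocation, with no stratification factor mentioned.

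**The concern.** The Cox model and the primary test concern the same event, closure of the index ulcer. The plan says that ulcer area and disease duration should be adjusted for in the first and leaves them out of the second, which is the comparison that decides the trial. Eligible ulcers may differ 20-fold in area (20 / 1), and the endpoint is complete closure by a fixed date, so area may well matter. If it does, an unadjusted comparison has a larger variance than necessary, and a chance imbalance in ulcer size passes straight into the risk ratio. The same reasoning applies to VCSS and CIVIQ if their baseline values exist but are not used.

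**Working it through.** **Inputs from the protocol (Sample size; Data analysis; Randomization).** Healing 62.7% against 40.6%, difference 0.221; two-sided 5%; 80% power; 1:1; 190 evaluable; 240 after 20% dropout.

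**Inputs assumed, because the protocol gives none.** Combined prognostic strength of area and duration, as one standardised score: log-odds 0 to 1.2 per SD. Correlation r between baseline and follow-up score: 0.3 to 0.7.

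**Step 1. The plan's own figure.** With the pooled formula:

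- Mean rate = (0.627 + 0.406)/2 = 0.5165. Null term 2 × 0.5165 × 0.4835 = 0.4995. Alternative term 0.627 × 0.373 + 0.406 × 0.594 = 0.4750.
- n per arm = [1.96 × √0.4995 + 0.8416 × √0.4750]² / 0.221² = 1.965² / 0.0488 ≈ 79.1, so 80 per arm, 160 in total.

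Other two-sided forms give 154 (unpooled), 158 (arcsine) and 176 (continuity-corrected). The stated 190 is not reproduced, but it errs on the large side. The dropout step does reproduce: 190 / 0.8 = 237.5, close to 240.

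**Step 2. Power of the unadjusted test.** Power = Φ[(0.221 − 1.96 × √(0.4995/n)) / √(0.4750/n)].

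- n = 95: (0.221 − 0.1421) / 0.0707 = 1.116, power 86.8%.
- n = 120: (0.221 − 0.1264) / 0.0629 = 1.503, power 93.4%.
- Fisher's exact test: 83.3% at 95 per arm, 90.8% at 120 per arm.

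All exceed 80%.

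**Step 3. Power after adjustment.** Simulation, 4,000 trials per row, with marginal rates held at 62.7% and 40.6%. Pearson chi-squared is compared with a logistic Wald test and with a standardised risk difference from the same logistic model (influence-function standard error). Monte Carlo error is about 0.5 point.

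| Per arm | Log-odds per SD | Chi-squared | Logistic | Standardised |
|---|---|---|---|---|
| 95 | 0 | 87.1% | 87.0% | 87.1% |
| 95 | 0.5 | 86.9% | 89.2% | 89.4% |
| 95 | 0.8 | 86.9% | 90.3% | 90.9% |
| 95 | 1.2 | 86.7% | 93.0% | 93.3% |
| 120 | 0 | 92.7% | 92.9% | 93.0% |
| 120 | 0.5 | 92.8% | 94.4% | 94.6% |
| 120 | 0.8 | 92.0% | 95.8% | 96.0% |
| 120 | 1.2 | 93.3% | 97.5% | 97.5% |

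For strengths of 0.5 to 1.2 the gain is about 2 to 7 points at 95 per arm and, measured against the formula value of 93.4%, about 1 to 4 points at 120 per arm. It is nil at strength 0.

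**Step 4. Type I error.** At 95 per arm under the null, the adjusted tests rejected in 4.9% to 5.9% of trials and chi-squared in 5.0% to 5.1%. The standard error of such a rate is √(0.05 × 0.95/4000) = 0.34 point. A further run at strength 0.8 gave 5.6% adjusted and 5.9% unadjusted, so a small excess from adjustment is possible but not established.

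**Step 5. Scores.** ANCOVA variance as a fraction of a follow-up-only comparison is 1 − r². As a fraction of a change-from-baseline comparison it is (1 − r²) / [2(1 − r)] = (1 + r)/2.

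| r | Against follow-up only | Reduction | Against change |
|---|---|---|---|
| 0.3 | 0.91 | 9% | 0.65 |
| 0.5 | 0.75 | 25% | 0.75 |
| 0.6 | 0.64 | 36% | 0.80 |
| 0.7 | 0.51 | 49% | 0.85 |

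**The case against.** The strongest reply is that nothing here is an error. In a 1:1 randomised trial a chi-squared or Fisher test with a risk ratio is valid for the stated endpoint, it matches the two-proportion basis of the sample size, and it is adequately powered. That stands. A reader might infer from the missing adjustment that the trial is underpowered; Step 2 shows that it is not. Nor do the documents contradict themselves: a simple primary test beside an adjusted Cox model is a common arrangement, and the Cox model will give some view of any imbalance in ulcer size.

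Several limits on the size of the gain also stand:

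- Analysis in the full analysis set, with the last observation carried forward for missing primary outcomes, puts the analysed number nearer 120 than 95 per arm, where the gain is smaller.
- The prognostic strengths are assumed. The 20-fold range is the eligibility window, not the distribution of enrolled ulcers, and duration of disease may not mean ulcer duration.
- A reader might infer that percent wound size change also ignores its baseline. It does not, because baseline area is in its definition. The ANCOVA point is confined to VCSS and CIVIQ.
- Those scores are listed only at 12 and 24 weeks, and the schedule figure is not shown, so their baseline collection cannot be confirmed.

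The reply that power is already sufficient is only partly an answer. The 22-point difference comes from a meta-analysis, and the abstract calls the existing evidence small and of low quality. If the true difference were 15 points (an assumption), chi-squared power at 95 per arm would be about 54%, and adjustment would raise it to about 57%, 60% and 62% at strengths 0.5, 0.8 and 1.0.

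**Conclusion.** The point holds as an efficiency improvement. The plan fixes an unadjusted primary comparison while naming, in the same section, baseline factors that it considers worth adjusting for when modelling the same event. On the stated rates the likely gain in power is about 1 to 4 points near 120 per arm and 2 to 7 points at 95 per arm, given a combined prognostic strength of 0.5 to 1.2 log-odds per SD; it is zero if the factors do not predict healing. The direction is secure in large samples, but the size rests on those assumptions. Adjustment also removes the effect of chance imbalance in ulcer size from the main estimate. For VCSS and CIVIQ the gain depends on baseline scores being collected: a variance reduction of 9% to 49% against a follow-up-only comparison for an assumed r of 0.3 to 0.7.

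**What to change.** Before unblinding, specify in the statistical analysis plan:

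1. **Primary analysis.** A logistic model for healing within 12 weeks with treatment, log baseline ulcer area and baseline duration of disease, stating whether duration refers to the ulcer or to the venous disease. Report the standardised (marginal) risk ratio with 95% CI, so that the effect measure stays the one now planned; the model's odds ratio would be a different quantity. Name the standard-error method and check its type I error at the planned size.
2. **Supportive analysis.** The chi-squared or Fisher test as now written.
3. **Covariates.** Baseline values only. Leave compression therapy and endovenous surgery out of this model unless they are fixed before randomisation; under Interventions both are part of standard care, and their timing is not stated.
4. **Scores.** If baseline VCSS and CIVIQ are collected, analyse the 12- and 24-week scores by ANCOVA on the baseline value.

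The cost is wording and programming, a commitment to one model form, and complete recording of the baseline covariates. Ulcer area and duration of disease are already needed for the Cox model, so the primary analysis needs no new data.

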## Background

Chronic venous disease (CVD) is a common pathology of the circulation system and is characterized by symptoms and signs as a result of structural or functional abnormalities of the veins. The most common symptoms and signs include pain, tightness, heaviness, feeling of swelling, reticular and varicose veins, edema, skin changes such as pigmentation, or ulceration [1]. CVD is often overlooked by healthcare providers because of an under-appreciation of the magnitude and impact of the problem, as well as incomplete recognition of the manifestations. In fact, CVD is a very common problem. A global survey suggested that the worldwide prevalence of CVD is 83.6%, with 63.9% of the subjects ranging from C1 to C6 [2]. In China, the prevalence of CVD is 8.89%, that is, there are nearly 100 million patients. The annual incidence rate is 0.5% to 3.0% [3].

Venous leg ulcers (VLUs) are defined as ulcers of the leg or foot that occur in the presence of venous disease. VLUs are the most severe manifestation of CVD. VLUs represent 80% of all leg ulcers [4]. The prevalence of VLUs is 1.5% in the general population in China [3], with a higher prevalence in the elderly [4]. Furthermore, VLUs are characterized by slow healing time and a high recurrence rate [5]. With the advent of global aging, more populations will be affected by VLUs. VLUs impose a heavy burden on patients’ physical and mental health and substantially reduce their quality of life. In addition, VLUs impose a heavy socioeconomic burden on patients, their families, and the health care system. Therefore, it is imperative to take efforts to improve the management of VLUs.

The main pathophysiology of VLUs is venous reflux or obstruction, venous hypertension, and chronic inflammation [6]. Conservative management is often the initial choice to reduce symptoms and protect against the progression of CVD. Given the severity and anatomic disorders of CVD, surgical and interventional methods are often reserved for unsatisfactory responses to conservative measures. Compression therapy is the mainstay of CVD [7]. Compression therapy can significantly improve symptoms and signs such as pain, swelling, skin pigmentation, activity, and well-being. For patients with ulcers, the benefits of long-term compression therapy have been repeatedly demonstrated in randomized trials. A healing rate as high as 97% can be achieved in those who are compliant with therapy [8].

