### Interventions

All patients will receive standard care of VLUs including compression therapy, sclerotherapy, and endovenous and surgical management. Other standard management such as treatment of infection, debridement, local wound care, anti-inflammatory analgesic drugs, dressings, and metabolic management will be prescribed as appropriate. Current guidelines were followed as per the attending clinician’s judgment [3, 5].

After randomization, participants will be given either pentoxifylline 400 mg twice daily or matched placebo (simulation agent of pentoxifylline) for 24 weeks. Because the dosage of pentoxifylline was 400 to 800 mg per day on the label of pentoxifylline in China, the dose in the trial was 400 mg twice a day. The micronized purified flavonoid fraction (90% diosmin and 10% other flavonoids) is currently one of the most widely accepted effective drugs for CVD and is also recommended by guidelines [17]. Thus, all patients in both groups will be dosed 450 mg diosmin twice daily for 24 weeks. Participants are prohibited from using fibrinolytic drug sulodexide and other venoactive drugs, such as aescin (horse chestnut extracts), coumarins, and low molecular weight heparin. All participants will be required to return the drug tablet to monitor the adherence. There will be no special criteria for discontinuing or modifying allocated interventions.

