### Sample size

The aim of this study is to investigate the effect of pentoxifylline on the wound healing rate of VLUs within 12 weeks. According to a recent meta-analysis, the wound healing rates of the pentoxifylline treatment and the control group were 62.7% and 40.6%, respectively [12]. A total of 190 participants will be required at the 5% significance level and 80% power. Assuming a drop-out rate of 20%, 240 participants will be included in this trial.

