## Discussion

Pentoxifylline is a readily available, safe, and inexpensive medication that was approved for the treatment of peripheral vascular disease. There were a few of clinical studies supporting a role for pentoxifylline in VLUs. However, the current studies enrolled a small number of subjects and were of short duration. This trial might provide more definite evidence that whether pentoxifylline could be an effective and safe therapeutic option for treatment of VLUs.

VLUs is the most common etiology of lower extremity ulcers followed by peripheral artery disease [4, 20]. It is postulated that the coexistence of both venous and arterial diseases accounted for 26% of patients with lower extremity ulceration [21]. This kind of mixed leg ulcer pose a particular challenge in clinical practice, because they are recalcitrant due to the different underlying pathologies [22]. However, due to the multiple effects of pentoxifylline on both venous and arterial disease, the results of this study might introduce a new choice for mixed arterial-venous ulcers.

Currently, the overall prognosis of VLUs is poor. Although compression therapy is the mainstay of CVD, supplementary therapy might have additional benefit. Combination therapy of venoactive drugs and other medications with different mechanism are usually considered in clinical practice. However, there was little evidence that support combination therapy for VLUs. Because the micronized purified flavonoid fraction (90% diosmin and 10% other flavonoids) is currently strongly recommended in the guidelines of CVD with moderate evidence [1], all subjects will be prescribed diosmin in this trial. The results of this study might provide evidence that whether the combination therapy of diosmin and pentoxifylline could have better effect than diosmin single drug treatment.

In this study, standard of care of VLUs is determined by the treating physicians and not protocolized. This is similar with real world practice. Thus, it is assumed that the results could have good generalization to the general Chinese population.

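### The Cox model lists compression therapy and endovenous surgery as covariates without limiting them to status at randomisation; coded from in-trial receipt, they could pull the adjusted hazard ratio towards 1

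*Protocol article*

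**What the plan says.** All references are to the protocol article.

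- **Covariates (Analysis of efficacy).** The Cox model is to be adjusted for "gender, age, duration of disease, BMI, pre-treatment ulcer area, compression therapy, and endovenous surgery". One of the seven, ulcer area, has a time label.
- **Care during the trial (Interventions).** "All patients will receive standard care of VLUs including compression therapy, sclerotherapy, and endovenous and surgical management". The same paragraph adds: "Current guidelines were followed as per the attending clinician’s judgment".
- **No standardisation (Discussion).** The authors state that "standard of care of VLUs is determined by the treating physicians and not protocolized".
- **When procedures are used (Background).** In chronic venous disease generally, "surgical and interventional methods are often reserved for unsatisfactory responses to conservative measures".
- **Place of the Cox model (Analysis of efficacy).** The primary comparison of 12-week healing is made "between the pentoxifylline group and the control group by chi-squared test or Fisher’s exact test", with a risk ratio. For time to healing, "Kaplan–Meier plot, Log-rank test, and Cox regression will also be used to analysis the time-to-event outcome", and a hazard ratio with 95% confidence interval will be reported.

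No section says whether the two therapies are entered as status at randomisation or as receipt during follow-up. The eligibility criteria mention neither earlier compression nor earlier venous surgery.

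**The concern.** Sex, age, disease duration, BMI and pre-treatment ulcer area are settled by the time a patient is randomised. Compression and endovenous surgery need not be. Where a clinician decides on a procedure by how the ulcer is doing, receiving it is partly a result of not having healed.

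An ever/never surgery indicator entered as a fixed covariate then raises two problems. A patient who heals early has less time in which to have the procedure, so the indicator carries information about time spent unhealed (immortal time). And if pentoxifylline speeds healing, fewer patients on it reach surgery, so adjusting for surgery removes part of the drug's effect.

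At stake is a hazard ratio that the article plans to report, with its confidence interval, as the adjusted effect of treatment on time to healing.

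**Working it through.** **1. Which reading does the text favour?** For in-trial receipt: the two therapies appear under Interventions in the future tense, their use is left to the clinician, and they lack the time label that ulcer area has. For baseline status: four other covariates in the list also lack a label and are plainly baseline values. The context leans towards in-trial receipt, but the text does not settle it.

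**2. Treatment effect for the simulation.** The article gives no figure for the Cox model to reproduce. From Sample size, "the wound healing rates of the pentoxifylline treatment and the control group were 62.7% and 40.6%, respectively". With exponential healing, weekly hazard = −ln(1 − p)/12:

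- pentoxifylline: −ln(0.373)/12 = 0.0822
- control: −ln(0.594)/12 = 0.0434
- hazard ratio (HR): 0.0822/0.0434 = 1.89

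**3. Simulation.** From the article: 1:1 allocation and 24 weeks of follow-up. Assumed, because the article gives nothing: surgery at 0.01 or 0.03 per week from week 4 among the unhealed; surgery with no effect on healing or doubling its hazard; log-normal patient heterogeneity (frailty) with SD 0 or 0.8. Surgery is either unrelated to prognosis or given at a rate inversely proportional to the patient's own healing hazard. Each scenario has 15,000 patients, and the Cox model is fitted with and without an ever-surgery term.

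True HR 1.89, surgery without effect on healing:

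| Who gets surgery | Frailty SD | Rate/week | Surgery, placebo / active | HR without term | HR with term | Change |
|---|---|---|---|---|---|---|
| Any unhealed patient | 0 | 0.01 | 10.5% / 6.8% | 1.787 | 1.759 | −2% |
| Any unhealed patient | 0 | 0.03 | 26.2% / 17.0% | 1.767 | 1.678 | −5% |
| Any unhealed patient | 0.8 | 0.01 | 9.4% / 6.7% | 1.596 | 1.581 | −1% |
| Any unhealed patient | 0.8 | 0.03 | 25.2% / 18.3% | 1.623 | 1.589 | −2% |
| Slow healers more often | 0 | 0.01 | 10.7% / 3.6% | 1.912 | 1.812 | −5% |
| Slow healers more often | 0 | 0.03 | 26.0% / 10.3% | 1.898 | 1.656 | −13% |
| Slow healers more often | 0.8 | 0.01 | 15.0% / 6.8% | 1.618 | 1.495 | −8% |
| Slow healers more often | 0.8 | 0.03 | 31.4% / 16.3% | 1.633 | 1.380 | −15% |

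Change is HR with term / HR without − 1; for the last row, 1.380/1.633 − 1 = −15%. Read each row across: both models use the same simulated patients, so the change is steadier than the level. The lower level at frailty SD 0.8 comes from the heterogeneity, not from the adjustment.

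If surgery doubles the healing hazard, the fall is 2–3% when surgery is unrelated to prognosis and 3–13% when slow healers get it more often.

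**4. Two controls.**

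- True HR 1.0: the HRs with and without the surgery term agree within about 1% in every scenario.
- True HR 1.89, surgery status fixed at baseline in about 30% of each arm: adjustment changes the HR by 0 to +4%, so there is no attenuation.

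**5. At the trial's own size.** 240 patients, conditional HR 1.89, frailty SD 0.7, surgery unrelated to prognosis and without effect, 500 trials per rate:

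| Rate/week | HR without term | HR with term | Power of the Cox test | Estimated surgery HR (truth 1.0) |
|---|---|---|---|---|
| 6% | 1.67 | 1.59 | 92% to 85% | 0.30 |
| 3% | 1.68 | 1.64 | 93% to 87% | 0.37 |
| 1% | 1.67 | 1.66 | 92% to 91% | 0.42 |

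The top rate is extreme: of patients unhealed throughout 24 weeks, 1 − exp(−0.06 × 24) = 76% would have had surgery; at 3% it is 51%.

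**The case against.** The strongest reply is that the article never says the two covariates are coded from in-trial receipt. Ulcer area may carry its label only because it is measured again as an outcome. A separate statistical analysis plan is announced and may define the coding. If it means status at randomisation, the attenuation disappears. This stands, and it makes the point conditional. It does not remove it: the article itself prescribes the covariate list, and two analysts following that list could fit different models, one of them conditioning on post-randomisation care.

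Second, the trial's main result is not exposed. This stands in full. A reader might infer that the primary conclusion is compromised, but that comparison is unadjusted, as are the log-rank test and the Kaplan–Meier plot. The power figures above are for the Cox test, whereas the trial was sized on 12-week proportions.

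Third, the size rests on assumptions. This also stands: the surgery rates, the frailty and the link between prognosis and surgery are all assumed. The Background says only that procedures are often held back for poor responders. It does not say that early healers never have one, and the Interventions text allows early use.

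Fourth, only surgery was simulated. Nothing in the article shows that use of compression depends on response or would differ by arm, so no size can be put on that term.

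**Conclusion.** The point holds in conditional form. If compression and endovenous surgery are coded from in-trial receipt, the adjusted Cox model conditions on post-randomisation events that can depend on healing. Should pentoxifylline work, the adjusted hazard ratio would be attenuated by about 1–5% when surgery is unrelated to prognosis and 3–15% when slow healers receive it more often. These figures concern surgery alone and depend on the assumed rates.

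Three stronger readings are not supported. The article does not establish that the hazard ratio is biased, because it leaves the time point open. The distortion does not manufacture a benefit: there is essentially none under no drug effect, and otherwise it runs towards 1. And although the surgery coefficient would look harmful when it is not, the article announces no inference about surgery, so that is a side effect rather than a flaw in the randomised comparison.

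Because only a supportive estimate is at risk, this should be fixed but is not critical.

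**What to change.** State in Analysis of efficacy, and carry into the statistical analysis plan, that Cox covariates are restricted to values fixed before randomisation: sex, age, disease duration, BMI, baseline ulcer area and, if recorded, compression or endovenous surgery status at randomisation. Drop in-trial compression and endovenous surgery from the model and report both descriptively by arm.

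The cost is one sentence. Dropping the in-trial terms needs no new data and alters neither the sample size, the primary analysis nor patient care. The baseline versions of the two terms can be used only if that status is collected.

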### Withdrawal of individual subjects

Subjects can leave the study at any time for any reason. The trial should be suspended in a special subject in the following conditions: (1) serious adverse events relevant or not relevant to pentoxifylline occur, (2) suffer from acute life-threatening disease, (3) death, and (4) violate the trial protocol, which influenced the evaluation of the endpoint.

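### VCSS and CIVIQ, measured at weeks 12 and 24, are compared by simple two-group tests with no missing-data rule of their own, and TNF-α and IL-6 are left out of the secondary comparison

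*Protocol article*

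**What the plan says.** Under Secondary outcomes the protocol article lists healing rates at other time points, percent wound-size change at week 12, TNF-α and IL-6 at weeks 4, 12 and 24, VCSS and CIVIQ at weeks 12 and 24, and recurrence.

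Analysis of efficacy assigns the healing rates at other times to time-to-event methods. For the rest it states: "The secondary analysis will compare the VCSS score, CIVIQ score, percent of wound size changes, and ulcer recurrence within 24 weeks by" a t test, Wilcoxon test, chi-squared test or Fisher's exact test as appropriate. The cytokines are in neither group.

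The same section has one missing-data rule: "Last observation carried forward will be used to fill up the missing values if some primary outcomes may be missing".

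Three other statements bear on the point:
- Data analysis: "All analyses will be conducted in the full analysis set (FAS) population", with the per-protocol set assessed as well.
- Data analysis: "An independent statistical analysis plan will be formulated".
- Sample size: "Assuming a drop-out rate of 20%, 240 participants will be included in this trial".

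**The concern.** The method for the two clinical scores is fixed, not left open. A t or Wilcoxon test at week 24 compares the patients who have a week-24 value and ignores the week-12 value already collected from the same patients and from those who left in between. With 20% drop-out planned, this loses information. If drop-out is related to outcome differently in the two arms, the comparison can also be biased.

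The missing-data rule does not help, because its own wording confines it to the primary outcome.

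The cytokine gap is an internal mismatch. Every other listed secondary outcome is given a method. TNF-α and IL-6, which carry the anti-inflammatory rationale set out in the Background and are named again in the Abstract, are not.

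At stake are the precision and credibility of the week-24 severity and quality-of-life results, and whether the mechanistic outcome has a prespecified comparison.

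**Working it through.** **Figures from the documents.** 190/0.8 = 237.5, rounded up to 240, so the drop-out step is consistent. 240 × 0.8 = 192, or 96 per arm observed out of 120. The plan gives no power or variance for VCSS, CIVIQ or the cytokines, so there is no plan figure to reproduce for them.

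**Assumptions, not in the documents.** SD 1 at each visit. Correlations 0.5 (baseline with week 12), 0.4 (baseline with week 24) and 0.7 (week 12 with week 24). True week-24 effect 0.40 SD. Two-sided 5% level. All 20% are missing at week 24, and the timing of the loss is varied.

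**Power under random drop-out.** Power = Φ(0.40/SE − 1.96).

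- *t test at week 24:* SE = √(2/96) = 0.1443; 0.40/0.1443 = 2.771; power = Φ(0.811) = 79%.
- *Model with baseline, all losses after week 12:* variance given baseline = 1 − 0.4² = 0.84. R² on baseline and week 12 = (0.16 + 0.49 − 2 × 0.4 × 0.7 × 0.5)/(1 − 0.25) = 0.4933, so the residual variance is 0.5067 and week 12 carries 0.84 − 0.5067 = 0.3333. SE = √[2 × (0.5067/96 + 0.3333/120)] = 0.1269; power = Φ(3.151 − 1.96) = 88%.
- *Model with baseline, all losses before week 12:* only baseline helps. SE = √(2 × 0.84/96) = 0.1323; power = Φ(3.024 − 1.96) = 86%.
- *Model without baseline, all losses after week 12:* SE = √[2 × (0.51/96 + 0.49/120)] = 0.1371; power = Φ(2.918 − 1.96) = 83%.

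Simulation with 120 per arm agrees: about 79% for the t test and 85-89% for the baseline-adjusted model, depending on when patients leave.

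**Bias with no true effect.**

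- *Random drop-out in both arms:* bias 0, type I error 5%.
- *Same outcome-related mechanism in both arms:* both means shift equally and the shifts cancel; bias 0, type I error about 5%.
- *Worse placebo patients leave, active patients leave at random:* assume logistic drop-out with slope 1 per SD of the week-12 score and 20% overall. The mean week-12 score of placebo patients who stay is then 0.173 SD too good. At week 24 the shift is 0.7 × 0.173 = 0.121 SD. Type I error = Φ(−1.96 + 0.121/0.1443) + Φ(−1.96 − 0.121/0.1443) = 0.131 + 0.003 = 13%. Simulations gave 0.12 to 0.13 SD and 13-15%, so about 0.13 SD and 14%. The direction is against pentoxifylline.

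**What the model removes in that last case.**

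- *All losses after week 12:* bias 0.00 SD, type I error about 5%, because the week-12 score that drives drop-out is observed.
- *Half of the losses before week 12:* about 0.04 to 0.05 SD remains.
- *All losses before week 12:* the model has only baseline for these patients. Baseline corrects 0.4 × 0.5 × 0.173 = 0.035 SD, leaving 0.121 − 0.035 = 0.09 SD.

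**Effect of 0.40 SD, one-arm mechanism, losses after week 12.** In simulation the t test estimates about 0.28 SD with about 49% power; the model estimates 0.40 SD with about 88% power.

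**The case against.** The strongest objection is that this is a condensed article that announces a separate statistical analysis plan, and that handling of missing secondary data is commonly left to such a plan. That stands for missing-data detail as such. It does not cover a test that the article commits to, or a list of compared outcomes that leaves out one of its own listed outcomes.

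A second objection is that two-group tests on secondary scores are valid under randomisation and merely less efficient. That is correct when drop-out is random or acts alike in both arms, and the gain is then one of power only.

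A third is that the 20% was set for the 12-week endpoint, so much of the loss may come before week 12, where the model helps least. That also stands, and it is why the benefit is given as a range.

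Several stronger readings are tempting and are not supported:
- A reader might infer that the plan prescribes a completers-only analysis. It does not. It places all analyses in the full analysis set and is silent on missing secondary values. Use of observed cases at each visit is what the named tests lead to if nothing else is specified.
- A reader might infer that the week-24 results will be biased because patients leave for different reasons by arm. Different reasons are not enough: missingness must relate to the outcome differently by arm. Withdrawal of individual subjects includes "serious adverse events relevant or not relevant to pentoxifylline occur" among its grounds, but no document describes a pattern by arm.
- With outcome-related drop-out in opposite directions in the two arms, a simulation under somewhat different correlations (0.6, 0.6, 0.7) gave about 0.25 SD and 41% type I error. Nothing in the documents points to that pattern, so it is not used as the size of the problem.

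**Conclusion.** The point holds as an analysis choice that can be improved cheaply, together with one internal mismatch. The mismatch is the firmest part: TNF-α and IL-6 are listed secondary outcomes and are absent from the comparison. This does not show that they will go unanalysed, since the separate analysis plan may supply a test.

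For VCSS and CIVIQ, the named tests leave the week-12 value unused at week 24. The power cost is about 6 to 10 percentage points (79% against 85-89%) if baseline scores are available, and less if they are not. Bias is possible, not established. Repeated-measures modelling reduces it, but removes it fully only when losses follow week 12 and depend on what has been observed.

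All sizes rest on the assumed correlations, effect and drop-out mechanism; only the 20% and the 240 come from the documents. Percent wound-size change is a single week-12 measure and lies outside this point. The primary outcome is untouched.

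**What to change.** In Analysis of efficacy and in the statistical analysis plan:

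1. Replace the t and Wilcoxon tests for VCSS and CIVIQ by one likelihood-based repeated-measures model per outcome, with arm, visit, arm-by-visit interaction, the baseline value where collected, and unstructured covariance. Report the week-12 and week-24 differences with 95% confidence intervals. Keep the Wilcoxon test as a sensitivity analysis.
2. Add TNF-α and IL-6 to the list of secondary comparisons, on the log scale at weeks 4, 12 and 24, with the same model.
3. State that missing VCSS, CIVIQ and cytokine values are handled through this model under missing-at-random.

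The cost is wording and modest programming in the SAS version already named, with no new data. The drawback is reliance on missing-at-random, which early drop-out related to unobserved healing would violate.
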